### Methods

#### Sample

The second study will be conducted in Serbia. The sample will be comprised of parents and caregivers that participated in Study 1, and additionally an equal number of non-parents. Non-parents will be matched with parents who participated in Study 1 in terms of their age, gender and education. To estimate the sample size needed for the second study, special attention was paid to the minimization of Type II error. The analysis results of the test strength show that detecting a statistically significant outcome bias effect by a bivariate analysis of variance (at level *p* < 0.01) of the effect size of.7, as reported by Baron and Hershey (1988), for a sample of 20 subjects per experimental group amounts to 99.9%.

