### Methods

#### Design, sample, and procedure

Participants will be parents or primary caregivers of children that are of the recommended age to receive vaccinations from their corresponding countries across Europe and Asia (i.e., Finland, Germany, Hong Kong, the Netherlands, Serbia, Slovenia, and Spain). Participants must be (a) over 18 years old, and (b) a parent or care taker of at least one child under the age of 12 years (Salmon et al., 2005; Jones et al., 2012).

The sample size will be a minimum of 222 participants per country, based on a power analysis for an effect size of 0.15, and 20 predictors in a linear multiple regression model. The final sample size will not have a difference greater than 10% between each country. To make sure that there aren't any significant differences between the sample sizes of the different countries, if the sample of any country exceeds 10% of the mean, some participants will be randomly discarded until the criterion is met.

The questionnaire is programmed in JavaScript and will be administered online. To take part in the study, participants will need an electronic device with access to internet. The link with an unbiased invitation letter will be posted on different social media platforms, forums and websites, targeting a wide range of parents from the entire vaccine-hesitancy spectrum. Once the link is opened, participants will first be given a brief introduction of the study. Participants will then read and sign an informed consent, which states they are able to halt and withdraw from the study at any moment without providing a reason, and that they agree for their anonymized data to be analyzed for future publications. Participants will be asked to compose a unique identification code (consisting of their parents' initials, and month of birth), which will be used to identify their data if they decide to withdraw their data after completing the study. After that, participants will be asked to provide their demographic information and complete a battery of vaccination- and decision-making-related questions, with a total of 115 items (the complete battery is in Appendix 1). Participants will be able to leave items unanswered. The study will take ~25 min to complete, but will vary depending on participants' speed of responding. This procedure was ethically approved by the Institutional Review Board of the Faculty of Philosophy at the University of Belgrade.

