#### Outcome bias

People make and evaluate their own and other people's decisions every day, but different timings of these two cognitive processes lead to differences in available information (Baron and Hershey, 1988). All possible outcomes of a decision are mutually exclusive. In the moment of making a decision, the winning outcome and following consequences could not have been known to the decision maker, but these two factors are what the evaluator is familiar with. The outcome of a decision, however, should not be taken into account when evaluating the decision, because this information is irrelevant to the quality of the decision. The systematic tendency to evaluate the quality of a decision based on the outcome is called outcome bias (Baron and Hershey, 1988). People tend to use their knowledge about the outcome in an aforementioned, not logically justified manner (Allison et al., 1996; Gino et al., 2010), and judge the discernment and competence of decision makers based on it (Berg-Cross, 1975; Baron and Hershey, 1988; Lipshitz, 1989; Gino et al., 2010). However, there is no evidence on the relationship between the outcome bias and vaccine hesitancy, or outcome bias' connectedness to the level of parental involvement in the decision.

In the second study, involvement will be decomposed into three aspects: the situation decision makers are deciding about, decision makers' role, or who is a protagonist (parents vs. non-parents), and finally, low and high involvement health situations. Because the importance of the decision is related to susceptibility to cognitive biases, we expect that higher involvement among parents, compared to non-parents, will lead to greater proneness to making biased evaluations in health, but not in non-health related dilemmas (experiment 1). In a similar manner, parents will be more susceptible to outcome bias in both high and low involvement situations than non-parents (experiment 2). However, we expect that in dilemmas where the parents are the protagonists, the outcome bias will be stronger in non-parents (experiment 3).The results will help to understand the specific role of parents in vaccine decisions and will also contribute to the research about the relationship between vaccine hesitancy and cognitive biases, which at the current state is often hypothesized about, but lacking in papers.

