### Proposed analysis

The aim of this study is to investigate the moderating role of involvement in susceptibility to outcome bias.

Like in study 1, different samples will be treated separately. We will be using R and Matlab to conduct our analysis.

There is a possibility that participants might remember their answer from the first session and adapt their answer in the second session accordingly. To control this, we will use a two-way ANOVA. We will test whether the order of presentation of the stimuli, particularly whether the positive or negative outcome presented first, has an influence on the answers obtained during the second session.

To test our hypotheses, we will use a bivariate analysis of variance with repeated measures. As measures of the outcome bias, the difference between mean evaluations of decisions with positive and negative outcomes will be used to form 2 new variables for each of the 3 experiments. These new variables will then be used in the analysis. We will verify the assumption of standard distribution by conducting a Kolmogorov-Smirnov Test. If we cannot assume standard distribution, we will use the Wilcoxon signed rank test instead of an ANOVA. Effect sizes for each pair of tasks will be presented as Cohen's D.

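### Study 2's 99.9% power is for detecting outcome bias itself; no power is given for the parent versus non-parent differences in bias that the study sets out to test

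*Protocol article*

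**What the plan says.** All references are to the protocol article.

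- **Study 2, Sample.** The power calculation is for "detecting a statistically significant outcome bias effect by a bivariate analysis of variance", "at level *p* < 0.01", "of the effect size of.7" (taken from a cited study), and "for a sample of 20 subjects per experimental group amounts to 99.9" per cent. The article presents it as the result of special attention to Type II error. It does not say which metric the 0.7 is in.
- **Study 2, Proposed analysis.** "The aim of this study is to investigate the moderating role of involvement in susceptibility to outcome bias". The analysed variable is the positive-minus-negative difference in mean ratings, two such variables per experiment.
- **Study 2, Outcome bias.** All three hypotheses compare parents with non-parents on the size of the bias. In experiment 1, higher involvement among parents "will lead to greater proneness to making biased evaluations in health, but not in non-health related dilemmas (experiment 1"). In experiment 2, parents are expected to be more biased at both involvement levels. In experiment 3, the bias is expected to be stronger in non-parents when the protagonists are parents.
- **Study 2, Design.** The experiments are mixed, with parents and non-parents as the two participant groups.
- **Study 2, Sample, again.** "The sample will be comprised of parents and caregivers that participated in Study 1, and additionally an equal number of non-parents". For Study 1, "The sample size will be a minimum of 222 participants per country".

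**The concern.** The effect that was powered and the effects to be tested are different. Outcome bias is a within-person contrast between positive- and negative-outcome versions of a task. The hypotheses ask whether the size of that contrast differs between two independent groups, and in experiments 1 and 3 whether that group difference itself depends on domain or protagonist. A between-group difference in a difference score is usually smaller than the score itself, and it is estimated with more error.

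The powered question is also already answered: the pilot found a clear outcome bias in 49 parents (F = 283.239, p < 0.001, mean Cohen's D 0.957). A reader of the Sample section would take Type II error to be negligible. If the study ran with numbers near 20 per group and found no moderation, that result could be read as evidence against the idea in the Joint discussion that parents are a special group, when it would say little either way.

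**Working it through.** **Inputs from the article:** effect size 0.7 (metric unstated); alpha 0.01 (sidedness unstated, two-sided taken); 20 per experimental group; stated power 99.9%; parents and non-parents in equal numbers; Study 1 minimum 222 per country; pilot N = 49, F = 283.239.

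**Assumed:** correlation 0.5 between a person's two ratings; a group difference in bias of 0.3 to 0.7 SD of the bias score. The Outcome bias section says there is no evidence linking outcome bias to parental involvement, so the documents supply no moderation effect.

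**Step 1: reproduce 99.9%.** Repeated-measures F test of positive versus negative outcome, m = 2 measurements, f = 0.7, correlation ρ = 0.5, N = 20:

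λ = f² × N × m / (1 − ρ) = 0.49 × 20 × 2 / 0.5 = 39.2, on 1 and 19 df, alpha 0.01. Power = 99.90%, which matches.

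The match depends on the metric and the correlation. With f = 0.7, ρ = 0.3 gives 98.7% and ρ = 0 gives 92.7%. If 0.7 is instead a standardised mean difference (f = 0.35, ρ = 0.5), λ = 9.8 and power is 61.1% for N = 20; reaching 99.98% then takes 80 people.

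**Step 2: power for the tested contrast.** For a parent versus non-parent difference of δ SD in the bias score, with n per group, use the two-sample t test with df = 2n − 2 and noncentrality δ√(n/2). For n = 20 this is 3.162 × δ on 38 df; the two-sided critical value at alpha 0.01 is 2.712.

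| δ (SD) | noncentrality, n = 20 | power, alpha 0.01 | power, alpha 0.05 |
|---|---|---|---|
| 0.3 | 0.95 | 4.8% | 15.2% |
| 0.35 | 1.11 | 6.5% | 19.0% |
| 0.5 | 1.58 | 14.4% | 33.8% |
| 0.7 | 2.21 | 32.3% | 57.8% |

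Solving for 80% power at n = 20 gives δ = 1.13 at alpha 0.01 and 0.91 at alpha 0.05.

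**Step 3: use the article's own effect.** The reading that gives 99.9% implies a mean difference of 2f = 1.4 rating SDs. The SD of the difference is √(2(1 − 0.5)) = 1 rating SD, so the bias is 1.4 SD of the bias score. With 20 per group and alpha 0.01:

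- bias a quarter smaller in one group: δ = 0.25 × 1.4 = 0.35, power 6.5%;
- bias halved in one group: δ = 0.5 × 1.4 = 0.7, power 32.3%;
- bias wholly absent in one group: δ = 1.4, power 95.1%.

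Even the most extreme moderation does not reach 99.9%.

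**Step 4: differences of differences.** If the groups differ by d SD in one domain only and a person's two bias scores have correlation r, the standardised contrast is δ = d / √(2(1 − r)). With r = 0, d = 0.35 gives δ = 0.247 and d = 0.7 gives δ = 0.495; 20 per group at alpha 0.01 then gives 3.4% and 14.1%. With r = 0.5, δ = d and the figures of Step 2 apply.

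**Step 5: effect of the number per group** (alpha 0.01, simple group difference, same formula):

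| n per group | δ = 0.3 | δ = 0.35 | δ = 0.5 | δ for 80% power |
|---|---|---|---|---|
| 20 | 4.8% | 6.5% | 14.4% | 1.13 |
| 40 | 10.3% | 14.8% | 34.9% | 0.78 |
| 100 | 31.8% | 45.2% | 82.4% | 0.49 |
| 222 | 71.7% | 86.4% | 99.6% | 0.33 |

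**The case against.** **The 99.9% is not an arithmetic error.** It reproduces under a repeated-measures test, which is the stated type of analysis, and each person sees both outcomes. A reader might infer from the Cohen's D reported elsewhere that 0.7 must be a d and that the figure is therefore wrong. The documents do not support that: D is used there for pairs of tasks, while the power sentence concerns an analysis of variance and names no metric. What follows is only that the metric should be stated.

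**The low power figures are conditional.** The 0.3 to 0.7 SD range is assumed, and alpha 0.01 appears only in the power sentence for outcome bias. The pilot allows a more favourable scale: √(283.239 / 49) = 2.40 SD of the difference score, if the F has 48 error df. On that scale a 40% difference in bias is 0.96 SD, with 63% power at 20 per group and alpha 0.01, and a 50% difference is 1.20 SD, with 85%. The pilot averaged 24 task pairs per person, so fewer tasks may give a smaller standardised bias. This shows how sensitive the result is to the assumed effect; it does not show adequate power.

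**Twenty may not be the sample.** A reader might infer that Study 2 will be run with 20 per group and will fail, or that 20 contradicts 222. Neither follows. The article never calls 20 a recruitment target; it can be read as a number shown to be enough for outcome bias. Nor can 222 per group be assumed: Study 1 parents are only invited, and two sessions on site in Belgrade are required.

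None of this touches the central point, that the power statement concerns a different effect from the hypotheses.

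**Conclusion.** The point holds in this form: the sample-size justification for Study 2 is attached to the wrong contrast. That rests on the text alone and needs no assumption. The size of the gap does need assumptions: a moderation effect of 0.3 to 0.7 SD, equal groups, a two-sided two-sample test on the bias score, and 20 per group. Under these, power is 5% to 32% at alpha 0.01 and 15% to 58% at alpha 0.05, and the group-by-domain and group-by-protagonist contrasts can have less. It cannot be concluded that Study 2 is underpowered, because the number per group is not fixed: between 20 and 222 per group, power at 0.35 SD runs from 6.5% to 86% at alpha 0.01.

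**What to change.** In Study 2, Sample:

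1. Stop using the 20-per-group, 99.9% sentence as the justification for Study 2. If it stays, label it as power for outcome bias only, and state the metric of 0.7 and the assumed correlation.
2. State the planned number of parents and of non-parents.
3. State the alpha for the hypothesis tests and the smallest group difference in bias that would matter.
4. Give power or the minimum detectable difference for each tested contrast: the parent versus non-parent difference in bias score, and the group-by-domain and group-by-protagonist differences of differences, with the assumed correlation between the two bias scores.
5. Show these over a range of attendance from 20 to 222 per group, since attendance at both sessions is not known in advance.

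The cost is a few rewritten sentences and a small table. No participants are added, but the stated power will be less favourable than 99.9%.

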#### Design

This study will comprise of three experiments, by which we aim to decompose the parental involvement in a more detailed manner, to test if it moderates susceptibility to outcome bias in parents. Specifically, we will test if parents differ in biased reasoning from non-parents (experiment 1), do those two groups differ when judging about involving decisions (experiment 2), and finally do parents show higher understanding for other parents' decisions, in comparison with non-parents as judges (experiment 3). The design of all three experiments is mixed, 2 × 2 with two groups of participants, parents and non-parents.

Experiment 1 (Parenting and biased reasoning): 2 (levels of domain: health and non-health) × 2 (outcomes).

Experiment 2 (Parenting and involvement): 2 (levels of involvement) × 2 (outcomes)

Experiment 3 (Parenting and solidarity): 2 (levels of protagonists: parents and non-parents) × 2 (outcomes).

The independent variables, the domain, level of involvement in the decision, and protagonist will have two levels: health (e.g., Vitamin supplementation) and non-health domain (e.g., free time); low (e.g., should protagonist give a vitamin supplement to a child or not), and high involvement (e.g., should protagonist vaccinate a child or not); and who is making a decision (parent as protagonist or non-parent as protagonist). The outcome variable will have two levels: the positive and the negative outcome. By crossing two levels of each binary independent variable in all three experiments (domain, involvement, decision maker) with the parenthood of participants (parents and non-parents), four experimental situations will be formed: parents in, e.g., high involvement situation, parents in low involvement situation, non-parents in high involvement situation, non-parents in low involvement situation (see Table 2). Every situation will be formed with both outcomes (see Table 3). Equivalent design will be applied in all three experiments.

**Table 2 T2:** Experimental situations in all three experiments.

	**Experiment 1 (domain)**		**Experiment 2 (involvement)**		**Experiment 3 (protagonist)**	
Factor levels	H	nH	hI	lI	P	nP
Parents	P × H	P × nH	P × hI	P × lI	P × x P	P × nP
Non-parents	nP × H	nP × nH	nP × hI	nP × lI	nP × P	nP × nP

*H, health-related; nH, non health-related; hI, high involvement; lI, low involvement; P, parent; nP, non parent*.

**Table 3 T3:** Tasks for all three experiments.

	**Domain**		**Involvement**		**Protagonist**	
Factor levels	H	nH	hI	lI	P	nP
Positive outcome (+)	H+	nH+	hI+	lI+	P+	np+
Negative outcome (−)	H−	nH−	hI−	lI−	P−	nP−

*H, health-related; nH, non health-related; hI, high involvement; lI, low involvement; P, parent; nP, non parent*.

Each subject will participate in the procedure in two time slots, separated by 1 week (with opposite outcomes). For each experimental situation, a Latin square design will be used for randomizing the order of presentation of experimental tasks during two experimental sessions.

#### Stimuli and the third pilot study

The stimuli in this study will have the form of an evaluation task, principally used in judging and decision-making research paradigms. The text presented to the participant will consist of a prolog (a description of a situation that contains a dilemma), followed by explicitly stating which option the decision maker (DM; the protagonist of the presented situation) opted for, and the outcome of the decision. Outcomes of DM's decisions will be twofold: positive and negative. Participants' task will be to evaluate the presented decision by rating it on a scale from −3 to +3 [−3—the worst decision the DM could have made, +3—the best decision the protagonist (DM) could have made].

The third pilot study was conducted in Serbia, during December, with the aim to test items. The design was experimental, 2 (outcome) × 2 (involvement). By crossing factors of involvement and outcome, four categories of tasks were formed: high involvement with positive outcome, high involvement with negative outcome, low involvement with positive outcome, low involvement with negative outcome.

Participants were parents with pre-schoolers, younger than seven years old (*N* = 49, 73% female, mean age 34.88). Each participant was presented with 24 pairs of tasks consisting of a prolog, decision maker's decision, and the outcome of the decision in two time slots separated by two weeks. During the second session participants were presented with the same tasks but with outcomes opposite to those from the previous session. Participants' task was to evaluate the decision on a 10-point Likert scale (1 = the worst decision the DM could have made, 10 = the best decision the DM could have made).

Results showed that there was a statistically significant outcome bias detected on a sample as a whole [*F*_(1)_ = 283.239, *p* < 0.001]. Mean evaluation of stimuli with the positive outcome was 6.02 (*S* = 0.922), while the mean evaluation for stimuli with negative outcome was 3.56 (*S* = 0.834). The effect size coefficients were calculated for each pair of tasks. Cohen's D coefficients ranged from 0.223 to 1.604, with mean value of 0.957,

Based on these effect sizes, as well as on the analysis of participants' impressions about questions, a number of convenient stimuli will be selected for the Study 2 experiment.

#### Procedure

After successfully completing Study 1, the participants will be asked to take part in the experiment. The experiment will be conducted at the Faculty of Philosophy of University in Belgrade, in classrooms equipped with computers. The non-parent sample will be collected separately, from the available pool of participants from general population in database of partner institution. Participants will, again, have a self-generated personal code as their identification. Each subject will be provided with an introductory explanation for the following part of the study and given detailed instructions. Each participant will read a prolog (the situation), the decision the protagonist made and the outcome of the decision will be explicitly stated, and then participants will evaluate that decision. This process will be repeated twice. After finishing the second round, participants will be asked to give consent to store and use the data obtained in the current session, then they will be presented with a thank you note along with a reminder to visit the venue again in a week. They will also be asked to provide their e-mail address to enable us to send them a reminder, and, if they wish, a personal result, in comparison with both samples. After completing the task in the following week, participants will be asked to give consent again, presented with a thank you note, and the authors' email addresses if they have any inquiries regarding the experiment. Debriefing will be provided immediately, with the repeated emphasis that the situations described in the tasks are simulations and that they are not based on real data. The procedure was ethically approved by the Institutional Review Board of the Faculty of Philosophy at the University of Belgrade.

### Proposed analysis

The aim of this study is to investigate the moderating role of involvement in susceptibility to outcome bias.

Like in study 1, different samples will be treated separately. We will be using R and Matlab to conduct our analysis.

There is a possibility that participants might remember their answer from the first session and adapt their answer in the second session accordingly. To control this, we will use a two-way ANOVA. We will test whether the order of presentation of the stimuli, particularly whether the positive or negative outcome presented first, has an influence on the answers obtained during the second session.

To test our hypotheses, we will use a bivariate analysis of variance with repeated measures. As measures of the outcome bias, the difference between mean evaluations of decisions with positive and negative outcomes will be used to form 2 new variables for each of the 3 experiments. These new variables will then be used in the analysis. We will verify the assumption of standard distribution by conducting a Kolmogorov-Smirnov Test. If we cannot assume standard distribution, we will use the Wilcoxon signed rank test instead of an ANOVA. Effect sizes for each pair of tasks will be presented as Cohen's D.

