### Proposed analysis

We will use statistical software (Matlab, R) for data analysis. We will analyse samples from each country separately because the differences in terms of language, legal framework in relation to vaccines, demographical characteristics and representativeness make the comparability between the different samples, and thus, their conjugate analysis, difficult (Ember et al., 1998).

For each sample, a factor analysis will be conducted to reduce the number of factors and control for interrelatedness of the variables. Two clusters of variables will be included: demographics (age, education level, number of children, mean age of children), and vaccine-related decision constructs (scores on scales on vaccination, vaccine hesitancy, perceived freedom of the decision, choice overload, actively open-minded thinking, trust toward authorities, availability of relevant information, perceived scientific consensus on vaccination, subjective estimation of percentage of children vaccinated on the country, perceived social consensus on vaccination, risk taking, and elaboration of potential outcomes). We expect the factor structure of each sample to be similar. With the reduced number of factors, a multivariate linear regression analysis will be conducted and the predictive power will be tested. The aforementioned factors will serve as predictors, and the parental intention to vaccinate (“I plan to vaccinate my child in accordance to the official vaccination schedule of my country”) will serve as criterion. All variables mentioned will also be included in a multivariate analysis of variance to see if there are differences between them depending on the level of adherence (total adherence, not completely total adherence, no adherence at all) to the official vaccination schedule of their children. We will test the proposed model of mediation (Figure 1) using regression analysis and compare it to a more complicated model with involvement as an additional factor.

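### Study 2 keeps Study 1's rule of treating samples separately, although its only samples are the parents and non-parents that its hypotheses compare

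*Protocol article*

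**What the plan says.** The rule comes near the start of Proposed analysis in Study 2: "Like in study 1, different samples will be treated separately". It refers back to Proposed analysis in Study 1, which reads: "We will analyse samples from each country separately". The reasons given there are differences between countries in language, vaccine law, demographics and representativeness.

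For Study 2, the Sample section says: "The second study will be conducted in Serbia". It describes the participants as "parents and caregivers that participated in Study 1, and additionally an equal number of non-parents". The Procedure section states that "The non-parent sample will be collected separately" and offers each participant "a personal result, in comparison with both samples".

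The Design section says: "The design of all three experiments is mixed, 2 × 2 with two groups of participants, parents and non-parents". It crosses domain, involvement and protagonist with the parenthood of the participants.

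The hypothesis test in Proposed analysis is a repeated-measures analysis of variance, described as bivariate. It uses two outcome-bias scores per experiment, each a difference between mean ratings under positive and negative outcomes. If normality cannot be assumed, the Wilcoxon signed rank test replaces it. No between-subject factor is named.

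**The concern.** A rule written for countries has been carried into a study with one country. The only groups left for it to act on are parents and non-parents, and each experiment exists to compare those two.

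If an analyst followed the sentence literally, the repeated-measures analysis would be run once in parents and once in non-parents. Each run can show whether that group has outcome bias, and whether the bias changes with domain, involvement or protagonist. Neither run tests whether parents differ from non-parents. A significant result in one group beside a non-significant one in the other could then be presented as moderation by parenthood, which it does not establish. The Joint discussion plans to treat supportive results as evidence that parents are a special group, so that conclusion needs a direct test.

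**Working it through.** The point turns on wording, so the sections are set side by side.

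**1. What the rule can apply to.** In Study 1 a sample is a country. Study 2 has one country (Sample section), so on the country meaning there is nothing to separate. The other meaning available in Study 2 is the one in the Procedure section, which speaks of a non-parent sample and of both samples. On that meaning the rule separates parents from non-parents.

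**2. What the hypotheses need.** Write B(g, c) for the mean outcome bias of group g (P parents, N non-parents) in condition c. The introduction to Study 2, under Outcome bias, predicts:

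- Experiment 1: B(P, health) − B(N, health) > 0, with no such difference for non-health. This implies a parenthood × domain interaction.
- Experiment 2: B(P, high) − B(N, high) > 0 and B(P, low) − B(N, low) > 0.
- Experiment 3: B(N, parent protagonist) − B(P, parent protagonist) > 0.

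Every contrast takes one term from each group.

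**3. What separate analyses give.** Within one group g, the analysis estimates B(g, 1), B(g, 2) and B(g, 1) − B(g, 2). None of the contrasts in step 2 is tested by these.

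**4. Whether the rest of the analysis section restores the comparison.**

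- The two scores per experiment are most naturally one per level of domain, involvement or protagonist, which is the repeated factor. This is my reading; the article does not spell it out.
- The two-way analysis of variance in the same section checks the order of presentation, not parenthood.
- The Wilcoxon signed rank test compares paired values, so it does not compare two independent groups.

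Nothing in the section states that parenthood enters the hypothesis test.

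**5. The power figure, as a side check.** The Sample section gives 99.9% power for the outcome-bias effect (effect size 0.7, p < 0.01, 20 per experimental group). It can be reproduced by a within-subject F test if 0.7 is Cohen's f and the correlation between repeated ratings is 0.5. Neither assumption is stated. Then λ = f² × N × m / (1 − ρ) = 0.49 × 20 × 2 / 0.5 = 39.2 on 1 and 19 degrees of freedom, and power is 0.9990. With ρ = 0.3 it is 98.7%, and with ρ = 0 it is 92.7%. The figure concerns outcome bias itself, not a difference between groups, so it does not settle which reading is meant.

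**The case against.** The best defence is that the sentence explains itself. It points to Study 1, where the separated samples are countries, and language and vaccine law give no reason to separate two groups living in one country. The abstract says that the studies run in eight countries, which suggests that the sentence is a leftover. The Design section calls the experiments mixed and crosses each factor with parenthood. Once outcome is collapsed into difference scores, the two factors of a bivariate analysis are plausibly condition and parenthood. A condensed article may also leave the full model to an analysis plan that is not shown.

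Most of this stands, and it limits the point. A reader might infer that parenthood never enters any model and that all three hypotheses will go untested. The article does not support that as fact, because it is only one of two readings and the Design section speaks against it. A reader might also want a rate of false claims of moderation. That would need the power within each group. At the stated 99.9%, a split result with equal true bias would occur 2 × 0.999 × 0.001, or about 0.2% of the time, and other assumed powers give other answers. No rate is claimed here.

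The defence does not rescue the sentence. On the country reading it is empty. On the other reading it conflicts with the design. It is also an explicit instruction, so it cannot be excused as detail left to another document.

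The Sample section does match non-parents to parents on age, gender and education. A signed rank test could compare the groups if the matching were one to one and the pairs were kept in the analysis. The article says neither, and such a test would still breach the rule.

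**Conclusion.** The point holds as an internal contradiction. The separate-samples sentence has no valid use in Study 2: it either applies to nothing, or it conflicts with the mixed design and blocks the parent versus non-parent comparison in all three experiments. The intended analysis is probably a joint one, but Proposed analysis does not say so, and its fallback test points the other way.

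The size is qualitative: the main hypothesis test of three out of three experiments is affected if the sentence is followed literally, and none if it is ignored. This rests on two readings: that the two scores per experiment correspond to the two levels of the repeated factor, and that the sample is confined to Serbia as the Sample section says. The abstract's eight-country wording for both studies is a clerical mismatch with no effect on the analysis.

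**What to change.** Delete the sentence from Proposed analysis in Study 2. State instead that, for each experiment, the two outcome-bias scores are analysed in one mixed analysis of variance, with parenthood as the between-subject factor and domain, involvement or protagonist as the repeated factor. Then name the test of each hypothesis:

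- Experiment 1: the parenthood × domain interaction, with parent versus non-parent contrasts within the health and non-health domains.
- Experiment 2: the parenthood effect, with contrasts at high and at low involvement.
- Experiment 3: the parenthood × protagonist interaction, with the parent versus non-parent contrast for parent protagonists.

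Any non-parametric fallback for the group comparison should be one for independent groups. As a clerical correction, the abstract should say that Study 2 is conducted in Serbia only.

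The cost is a short rewrite of one section and one phrase in the abstract. No extra data are needed, since both groups and all conditions are already planned.
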